## Methods

### Trial design

The trial is a four-centre, pragmatic [24] (Supplementary Table 1, Supplementary Fig. 1, Additional File 1) [25], pilot hybrid type 1 effectiveness-implementation trial with two parallel groups, randomized in a 1:1 ratio and stratified by centre in variable-sized blocks (ClinicalTrials.gov Identifier: NCT06650410). Participants will be randomized to the following: (1) immediate receipt of VIVA intervention or (2) wait-list usual care control and delayed receipt of VIVA 10-week post-randomization. The randomization sequence will be created and uploaded to REDCap by the trial statistician. Randomization will take place after the baseline assessment; the exercise professional delivering the intervention (not blind to allocation) will access the randomization function in REDCap to determine the participant’s allocation and communicate it to them. Outcome assessors will be blind to group allocation. Participants will not be blind to group allocation because they will know what group they are assigned to.

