#### Harms

We will ask participants to report changes in health status, falls, fractures, or any other injuries. All serious adverse events will be reported to research ethics boards and the central coordinating site in accordance with their requirements.

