### Recruitment and sample size

Our sample size for the current study was derived from an estimate of the required recruitment rate for the larger trial. For the future trial, a sample size of 54 in each of the intervention and control groups would allow us to detect between-group difference of two chair stands in the 30-s chair stand test with a standard deviation (SD) of 3.7 and power of 80%, which would be similar to what we have observed in prior studies of pre-frail older adults [28, 34], and is considered a minimal clinically important difference [35]. For the larger trial, we will inflate sample size by 15% to account for attrition, resulting in a sample size of 124 participants (~ 2 individuals per month, per site, across 5 sites over 13 months). To assess feasibility of recruitment in the current study, we plan to recruit 32 participants up to 5 months across 4 sites (8 participants per site). We chose a sample size of two individuals per site per month to retain the same recruitment rate as the future trial and allowed for an additional month of recruitment to be conservative. A sample size of 32 participants will also allow us to test the evaluation cut-offs for the feasibility outcomes of retention (min = 0.5, hypothesized = 0.80, required sample size = 19) and adherence (min = 0.5, hypothesized = 0.75, required sample size = 27) with an alpha level of 0.05 and power of 80% [36]. The minimal (min) values represent the lowest acceptable outcome for study feasibility, while the hypothesized values reflect the expected and satisfactory outcomes for success.

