### Analyses

All analyses (Table 7) will be performed using SAS version 9.2 (Cary, NC, USA). The reporting is guided by CONSORT, SPIRIT, SAGER, and SIITHIA guidelines [37–39]. See Table 8 for Template for Intervention Description and Replication (TIDieR) checklist and Additional File 2 for SPIRIT checklist. Participant characteristics will be reported using mean (standard deviation (SD)), median (interquartile range (IQR)), or count (percentage). For the primary outcomes, we will report recruitment, adherence, and retention using count and percentage (95% confidence interval [CI]). We will use descriptive statistics and narrative or graphical means to report reach, effectiveness, adoption, maintenance, and resource use outcomes for quantitative data using an intention-to-treat approach and use content or reflexive thematic analysis for qualitative data [40]. We will report the between-group difference in effectiveness and maintenance outcomes as mean (SD) or median (IQR), percent change, and 95% CI. Analyses of between-group differences will be exploratory, and no clinical inferences will be made. There will be no interim analyses or stopping rules.

**Table 7 Tab7:** Variables, hypotheses, outcomes, and methods of analysis

Variable	Criteria for feasibility/hypothesis	Outcome measure	Methods of analysis
Primary feasibility outcomes			
Recruitment	We will recruit 32 participants, 8 per site, in 5 months	Number of participants recruited at each site	Descriptive statistics
Adherence	Adherence to the rehabilitation sessions will be 75%	The proportion of scheduled sessions participant attended	
Retention	80% of our sample will complete the trial	The proportion of participants who complete the final assessment out of the total number of participants	
Secondary clinical/implementation outcomes			
Reach	N/A	• Number of participants categorized by PROGRESS-Plus factors • Number of individuals recruited who are ≤ 12-week versus > 12-week post-vertebral fracture • Number of people who attend outcome assessments in-person versus virtually	Descriptive statistics and narrative or graphical means

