Effectiveness: physical function and balance, pain, fear of movement, falls (number of falls and number of people who fall), falls efficacy, quality of life, mood, physical activity, nutrition risk	Exploratory	• 30-s chair stand test, side-by-side stand, semi-tandem stand, tandem stand • Brief Pain Inventory Short Form • Tampa Scale of Kinesiophobia • Monthly falls survey • Short Falls Self-Efficacy • QUALLEFO-41 • Patient Health Questionnaire-8 • Physical Activity Scale for Elderly • SCREEN-14	Descriptive statistics and narrative or graphical means
Harms	No difference between groups	• Self-report of adverse events	Descriptive statistics
Adoption	Exploratory	• Number of screened and enrolled participants per referral source • The length of time to obtain radiology reports and number of people with ambiguous radiology reports	Descriptive statistics and narrative or graphical means
Implementation	Understanding the experiences of individuals involved in the study and adherence to the intervention sessions to inform future trials	• Semi-structured interviews with participants and exercise professionals • Proportion of prescribed exercises adhered out of the total exercises prescribed via the Wibbi app, reporting directly to exercise professional or a log • Fidelity	Reflexive thematic analyses for qualitative data Descriptive statistics and narrative or graphical means for quantitative data
Maintenance	Exploratory	• Adherence to the exercise sessions at the end of 18-week follow-up for immediate group only	Descriptive statistics and narrative or graphical means
Resource use	Exploratory	• Cost	Descriptive statistics

**Table 8 Tab8:** Template for Intervention Description and Replication (TIDieR) checklist for the VIVA feasibility study

Item category	Description
Brief name	Virtual Intervention for Vertebral frActures (VIVA): Feasibility Study for a Multicentre Trial
Why	Vertebral fractures are the most common fracture due to osteoporosis. Guidance on management suggests that a rehabilitation intervention should include pain management, nutrition, exercise, and safe movement strategies in people with a vertebral fracture; however, it is not clear if implementing the intervention may improve outcomes. Thus, there is a need to conduct a trial to determine if a future randomized controlled trial testing the effectiveness and implementation of such intervention is feasible

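### Table 7 gives harms a no-difference hypothesis that has no criterion, sits badly with the plan's own exploratory rule, and cannot be assessed with about 16 people per arm

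*Protocol article*

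**What the plan says.** Table 7 (protocol article, Analyses) has a column for feasibility criteria or hypotheses. Effectiveness, adoption, maintenance and resource use are marked exploratory there. Reach has no entry, and implementation has a descriptive aim. Harms alone among the secondary rows predicts a between-group result: "No difference between groups". Its measure is "Self-report of adverse events" and its method is descriptive statistics.

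The Harms section describes what is collected: "We will ask participants to report changes in health status, falls, fractures, or any other injuries".

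The text of the Analyses section promises 95% intervals for the three primary outcomes, and then says: "We will report the between-group difference in effectiveness and maintenance outcomes as mean (SD) or median (IQR), percent change, and 95% CI". Harms are in neither list, and they are also absent from the sentence that lists the outcomes to be described. Falls do appear in the effectiveness row of Table 7, as "falls (number of falls and number of people who fall", and so come under the interval sentence. The same section states that between-group analyses are exploratory and that no clinical inference will be drawn from them.

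On size, Recruitment and sample size says "we plan to recruit 32 participants up to 5 months across 4 sites (8 participants per site", and Trial design specifies "two parallel groups, randomized in a 1:1 ratio and stratified by centre in variable-sized blocks".

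**The concern.** A prediction of no difference in harms is a between-group statement with clinical meaning. It appears in a plan that treats such comparisons as exploratory, and nothing says how it would be judged. The obvious way to judge it is to look at two columns of counts and note that they are alike.

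At this size, alike counts are weak evidence. Participants have had a vertebral fracture within two years and are prescribed balance and strengthening exercise, and the results are meant to inform a larger trial. A sentence saying that the harms hypothesis was met could be carried into that proposal as a safety finding that the data do not support. Outside falls, the article does not promise the interval that would show a reader how little had been established.

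**Working it through.** The plan states no event rate, margin or power for harms, so there is no figure of its own to reproduce.

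**Inputs**
- Total 32 (Recruitment and sample size), allocated 1:1 (Trial design): 32 / 2 = 16 per arm, approximately, because blocks vary in size within centre.
- Event counts: not in the documents. Equal counts of 0, 1, 2 and 3 per arm are used as illustrations.
- True event rates: not in the documents. Those in step 3 are assumptions, shown as a range.

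**1. What equal counts leave open.** The Wilson 95% limits for x of n, with p = x/n and z = 1.96, are [p + z²/2n ± z√(p(1−p)/n + z²/4n²)] / (1 + z²/n). When both arms have the same p, with Wilson limits l and u, the Newcombe interval for the risk difference is ±√((p − l)² + (u − p)²).

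For 3/16 v 3/16: p = 0.1875, l = 0.0659, u = 0.4301. The half-width is √(0.1216² + 0.2426²) = 0.271.

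For 0/16 v 0/16: p = 0, l = 0, u = 3.84 / (16 + 3.84) = 0.194. The half-width is 0.194.

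| Observed, each arm | 95% interval for the risk difference (points) |
|---|---|
| 0 v 0 | −19 to +19 |
| 1 v 1 | −23 to +23 |
| 2 v 2 | −25 to +25 |
| 3 v 3 | −27 to +27 |

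**2. What zero events in one arm leaves open.** Solve (1 − p)^16 = α for p. The one-sided 95% limit is 1 − 0.05^(1/16) = 0.171. The upper limit of the two-sided exact 95% interval is 1 − 0.025^(1/16) = 0.206.

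**3. How often a table would look like no difference when there is one.** No test is planned, so the relevant question is what a reader of a descriptive table sees. Let C and T be independent binomial counts with n = 16, for control and VIVA. The probability that T is at most C + 1 is Σ P(C = c) × P(T ≤ c + 1).

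| Assumed true rates, control v VIVA | VIVA shows at most one more affected person |
|---|---|
| 5% v 15% | 49% |
| 10% v 20% | 48% |
| 5% v 20% | 32% |
| 10% v 30% | 22% |
| 10% v 40% | 7.5% |

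A true doubling from 10%, or tripling from 5%, gives a near-equal table, or one favouring VIVA, about half the time. A very large true excess rarely does.

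**4. Whether a large observed excess would go unnoticed.** As a yardstick only, the smallest imbalances reaching two-sided 5% on Fisher's exact test at 16 v 16 are 5 v 0 (p = 0.043), 7 v 1 (p = 0.037) and 9 v 2 (p = 0.023). Imbalances of that order would be plain in any descriptive table.

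**The case against.** The strongest reply is that the Analyses section already forbids the misreading. Between-group comparisons are exploratory and carry no clinical inference, and that sentence is not confined to effectiveness. The cell can be read as a plain expectation; the article never mentions equivalence, non-inferiority or a safety conclusion. Harms are not among the three feasibility criteria, so no decision to proceed rests on the cell. Falls already get a between-group interval. Any pilot with 16 per arm would give intervals this wide, and the exact form of adverse event tables is commonly left to an analysis plan that is not shown.

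Most of this stands, and it is why the point is minor. A reader might infer that even a large excess of harm would be taken as confirming the hypothesis. The documents do not support that: no test or rule turns a non-significant result into confirmation, and a large observed excess would be visible (step 4). Nor does the article commit to a formal equivalence claim, and a feasibility study needs no margin.

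What the reply does not remove is the stated hypothesis. This is not an omitted detail: the article prints a null prediction for harms, treats that row differently from its neighbours, and elsewhere rules out the kind of inference that declaring it met would be.

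**Conclusion.** The point holds as a minor inconsistency. The harms entry has no criterion, conflicts with the exploratory status given to between-group comparisons, and cannot be assessed at about 16 per arm. The risk is that similar counts are reported as the hypothesis being met, when equal counts of 0 to 3 per arm are compatible with a true excess of about 19 to 27 percentage points.

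The intervals assume 16 per arm, all followed for harms; losses would widen them. The probabilities in step 3 also depend on assumed event rates. The reporting gap concerns adverse events, fractures and injuries other than falls.

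**What to change.** Change the harms cell in Table 7 to *Exploratory; no conclusion of equal safety*. Add to the Analyses text that, for adverse events, fractures and other injuries, the report will give per arm the number and percentage of participants affected with an exact 95% interval, and the risk difference with its 95% interval.

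Limit this comparison to the controlled period, from randomization until the delayed group starts VIVA at week 10. After that both arms have been offered the intervention, and a whole-study comparison would mix exposed and unexposed time. Events after that point can be listed separately without a between-group contrast. No margin or formal test is needed.

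The cost is one table cell and a line or two of text, on data the plan already collects. The price is a less favourable safety statement: it would show wide intervals instead of a hypothesis declared met.

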## Discussion

The trial will build capacity for patient-oriented approaches to rehabilitation and implementation science, and a proposal for a future multicentre trial of VIVA using clinical effectiveness and implementation outcomes, adapted to different methods of delivery (virtual, in-person, hybrid, telephone), languages (English, French), practice settings (acute care, outpatient, community), and provinces, increasing its relevance to a diversity of patients, healthcare providers, and policy makers. We will publish the results of the current trial in an academic journal and present the findings in webinars for patients and conferences for researchers and healthcare professionals. We will use the results to evolve the intervention and intervention materials for future research and implementation efforts. For example, members of our team developed a care model for vertebral fragility fractures with the Fragility Fracture Network that aligns with our intervention [41]. Future dissemination efforts may include a VIVA implementation toolkit that we can disseminate with national or international organizations focused on fracture prevention.

## Data Availability

Not applicable.

## Abbreviations

PWLE: People with lived experiences
VIVA: Virtual Intervention for Vertebral frActures
RE-AIM QuEST: Reach, Effectiveness, Adoption, Implementation, and Maintenance Qualitative evaluation for Systematic Translation
PROGRESS: Place, Race/ethnicity/culture/language, Occupation, Gender and sex, Religion, Education Socioeconomic status; Social capital
BPI-SF: Brief Pain Inventory Short Form
TSK: Tampa Scale of Kinesiophobia
QUALEFFO-41: Quality of Life Questionnaire of the European Foundation for Osteoporosis-41
PHQ-8: Patient Health Questionnaire-8
PASE: Physical Activity Scale for Elderly
QALY: Quality-adjusted life year
SD: Standard deviation
IQR: Interquartile range
CI: Confidence interval
